### Sample size determination

The sample size is determined considering both the intervention and control using a formula recommended for dichotomous outcome variable. We assumed that implementation of community based intervention program to prevent domestic VAW is superior as compared with the standard service [51]. In addition, we considered 5% margin of error, 95% significance level and 80% power.$$ N=2\times {\left(\frac{z_{1-\alpha }+{z}_{1-\beta }}{\mathrm{d}\hbox{-} {\delta}_0}\right)}^2\times p\times \left(1-p\right) $$

Where as; N is the sample size of each group, P is prevalence in standard intervention (control arm), d: the real difference between two treatment effects (d = P_o_-P_x_); 22%–9% = 13% = 0.13: study done in Uganda (22%) in the standard intervention group [52]; δ_0:_ statistical acceptable margin (5%); ɑ: significance level at 95% (ɑ = 1–0.95 = 0.05 = 1.645), ß_:_ 80% power (ß = 1–0.8 = 0.2 = 0.845. Then, 15% is added for potential non-achievements. Furthermore, due to the multistage sampling, design effect is considered to boost the power and precision that taken from the design effect of women experienced physical or sexual violence in the study area (Amhara region) in the last 12 months was 1.11 [53]. Eventually, a total 1269 women is obtained for the three arms (i.e. 423 for each group). The number of qualitative study participants will be determined by information saturation. However, a minimum 12 in-depth interviews and two focus group discussions (FGDs) (male versus female groups) which comprise 8–10 discussants will be conducted.

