### Sampling procedure

Multistage, stratified and systematic sampling will be used to recruit study participants at their permanent place of residence. Three districts are selected out of nine districts in Awi zone (comprehensive intervention, active comparison and control). Then, six sub-districts (two sub-districts from each district) will be selected purposefully considering appropriateness for intervention, resource, and geographical non-proximity to control information contamination between intervention and controls. Then, sub-districts will be stratified (urban versus rural) to control the awareness level, access to information and community traditional gender norm variability between urban and rural dwellers. After that, the sample of the group will be proportionally allocated to size of each selected sub-district. The number of eligible households for this study will be identified using the community based health extension workers registry. Eventually, systematic sampling will be employed to select actual study participants at household level. Unique code will be given to selected households for intervention monitoring and finally endline evaluation purpose. In the meantime, if two married women are present in one household, only one woman will be selected using lottery method for interview.

Purposive sampling method will be used to select study participants for in-depth interview, key informant interview (KII) and FGDs. Community leaders will be consulted and actively involved on the recruitment of the most knowledgeable community representatives for in-depth interview, KII and FGDs. It will be conducted to explore individual and community perception about domestic VAW, sex negotiation, decision making, community gender norm, wife beating attitudes and community responses.

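### The design effect of 1.11 does not fit two sub-districts of about 200 women per arm, so the stated 80% power is not supported

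*Protocol article*

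**What the plan says.** The section Sample size determination uses a two-proportion superiority formula with a margin. Its inputs are:

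- **Error rates:** "we considered 5% margin of error, 95% significance level and 80% power", with the z-value for alpha given as "1–0.95 = 0.05 = 1.645", which is a one-sided value.
- **Effect:** "22%–9% = 13% = 0.13: study done in Uganda (22%) in the standard intervention group".
- **Margin:** "statistical acceptable margin (5"%), subtracted from the effect.
- **Variance:** "P is prevalence in standard intervention (control arm"), so p = 0.22.
- **Allowance:** "15% is added for potential non-achievements".
- **Clustering:** a "design effect of women experienced physical or sexual violence in the study area (Amhara region) in the last 12 months was 1.11", justified by the multistage sampling.

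The result is 423 women per arm and 1269 in total.

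The section Sampling procedure gives one district to each arm and then says that "six sub-districts (two sub-districts from each district) will be selected purposefully". Each arm's sample is shared between its two sub-districts in proportion to their size. No ICC, cluster size or number of clusters enters the sample size calculation.

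**The concern.** A design effect is not a constant of a region. It depends on how many women are taken per cluster and on how alike women in a cluster are for the outcome in question. The figure of 1.11 describes a regional estimate. The trial compares arms made of two very large clusters each, which is a different layout.

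The outcome differs too. The borrowed figure covers physical or sexual violence, while Data processing and statistical analysis defines domestic violence as any of physical, psychological or sexual violence.

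The plan's own reasoning makes negligible clustering hard to assume. It stratifies by urban and rural residence because gender norms vary between them, and the intervention is built on the idea that community beliefs shape attitudes to violence.

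At stake is how a null result is read. If power is well below 80%, a non-significant difference may be taken as evidence of no effect when it may reflect low power.

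**Working it through.** **1. Reproduce the plan's figure.**
N = 2 × ((1.645 + 0.845) / (0.13 − 0.05))² × 0.22 × 0.78 = 332.5.
332.5 × 1.15 × 1.11 = 424.4. Rounding down along the way (332, then 381, then 381 × 1.11 = 422.9) gives 423. The stated 423 is reproduced, so the arithmetic is not in dispute.

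**2. Cluster size.**
Recruited: 423 / 2 = 211.5 per sub-district. Evaluable, with the 15% allowance removed: 423 / 1.15 = 367.8 per arm, or 183.9 per sub-district. Both are averages, because allocation is proportional to size.

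**3. ICC implied by 1.11.**
From DEFF = 1 + (m − 1) × ICC, ICC = 0.11 / (m − 1).
With m = 211.5: 0.11 / 210.5 = 0.0005. With m = 183.9: 0.11 / 182.9 = 0.0006.

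**4. Power at other ICCs.** The article gives no ICC, so the values below are assumptions. Evaluable numbers are used throughout (m = 183.9), with n_eff = 367.8 / DEFF.

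- Plan's contrast (margin, one-sided 5%): power = Φ(0.08 / √(2 × 0.1716 / n_eff) − 1.645).
- Plain contrast (no margin, two-sided 5%): power = Φ(0.13 / √((0.22 × 0.78 + 0.09 × 0.91) / n_eff) − 1.96).

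| Assumed ICC | DEFF | n_eff per arm | Plan's contrast | 22% v 9%, no margin |
|---|---|---|---|---|
| 0.005 | 1.9 | 192 | 60% | 95% |
| 0.01 | 2.8 | 130 | 47% | 84% |
| 0.02 | 4.7 | 79 | 33% | 63% |
| 0.05 | 10.1 | 36 | 21% | 34% |

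For scale: at ICC 0.001 the plan's contrast has 78% power.

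**5. Two clusters per arm.** The z-based figures treat the between-cluster variance as known. Comparing two clusters with two leaves 2 degrees of freedom, where the critical values are 2.92 (one-sided) and 4.30 (two-sided) instead of 1.645 and 1.96. By the non-central t distribution:

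- plan's contrast, one-sided, ICC 0.0005: about 50%;
- plain contrast, two-sided, ICC 0: about 71%, and lower at any positive ICC.

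**6. Would more women help?** With two clusters per arm, n_eff cannot exceed 2 / ICC. At ICC 0.01 that is 200, below the 332 that the formula needs. More women in the same sub-districts could not restore 80% for the plan's contrast at that ICC.

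**The case against.** **The margin.** A reader might infer that the trial could not show the planned 13-point difference. The documents do not support that. The low figures belong to a contrast of 8 points, left after the 5-point margin is subtracted. The analysis section relies on difference in differences, ratios with 95% confidence intervals and P below 0.05, and mentions no margin. A plain z-test of 22% against 9% still has 84% power at ICC 0.01. This objection stands, so both sets of figures are needed. It is limited by step 5: with two clusters per arm, the plain two-sided test does not reach 80% even at ICC 0.

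**The planned analysis.** The same women are to be interviewed again, and difference in differences can cancel stable differences between sub-districts. The relevant correlation is then that of the change, which may be smaller than that of levels. This also stands as a caveat. It does not rescue 1.11: the sample size formula compares two proportions, takes no credit for repeated measurement, and gives no correlation of change.

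**The ICCs are assumed.** True, and the size of the loss depends on them. The mismatch between 1.11 and the cluster size does not.

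**It is a pilot.** The article describes a pilot of feasibility and effectiveness, and the remedy changes wording only. That bears on urgency. It does not make the stated power correct.

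**Conclusion.** The concern holds in this form: 1.11 does not fit the trial's own layout unless the ICC is about 0.0005 to 0.0006, so the statement that 423 women per arm give 80% power is not supported. The error lies in carrying the design effect over to a different layout.

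Over assumed ICCs of 0.005 to 0.05, power runs from about 60% down to 21% for the plan's margin contrast, and from about 95% down to 34% for 22% against 9% without the margin. For the comparison of proportions that the formula describes, these are upper limits, because they ignore the 2 degrees of freedom. They rest on equal sub-districts of 184 evaluable women and on correlations of levels; the figures for a difference in differences could differ.

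The supportable statement about consequence is that a null result may reflect lower power than stated. Separately, each arm is one district, so district and intervention are confounded, and no design effect applied to the number of women removes that.

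**What to change.** In Sample size determination:

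1. Replace the sentence on 1.11 with DEFF = 1 + (m − 1) × ICC at the planned cluster size (about 211 recruited, 184 evaluable), and state the ICC assumptions.
2. Withdraw the claim that 423 per arm gives 80% power.
3. Restate power as a range over those ICCs, with and without the 5-point margin, and give the limit set by two clusters per arm beside it.
4. Add that the difference-in-differences analysis depends on the between-sub-district correlation of change, which may be smaller than that of levels. An ICC estimated from the baseline data of six purposively chosen sub-districts would be very imprecise and would describe levels, so it should not be relied on to settle the question.
5. State that no design effect removes the confounding of one district per arm, and that a null result may reflect lower power than stated.

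The cost is wording and a less favourable stated power. No extra enrolment is needed.

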### Sampling procedure

Multistage, stratified and systematic sampling will be used to recruit study participants at their permanent place of residence. Three districts are selected out of nine districts in Awi zone (comprehensive intervention, active comparison and control). Then, six sub-districts (two sub-districts from each district) will be selected purposefully considering appropriateness for intervention, resource, and geographical non-proximity to control information contamination between intervention and controls. Then, sub-districts will be stratified (urban versus rural) to control the awareness level, access to information and community traditional gender norm variability between urban and rural dwellers. After that, the sample of the group will be proportionally allocated to size of each selected sub-district. The number of eligible households for this study will be identified using the community based health extension workers registry. Eventually, systematic sampling will be employed to select actual study participants at household level. Unique code will be given to selected households for intervention monitoring and finally endline evaluation purpose. In the meantime, if two married women are present in one household, only one woman will be selected using lottery method for interview.

Purposive sampling method will be used to select study participants for in-depth interview, key informant interview (KII) and FGDs. Community leaders will be consulted and actively involved on the recruitment of the most knowledgeable community representatives for in-depth interview, KII and FGDs. It will be conducted to explore individual and community perception about domestic VAW, sex negotiation, decision making, community gender norm, wife beating attitudes and community responses.

### Measurement tools

Data will be collected using structured and semi-structured questionnaire that is adapted from various literature [29, 41, 50, 54–70]. The tool will be pretested and modified to suit with the local context. It will consist of demographic, socio-economic variables about the women, relationship, community and societal level factors of domestic violence. In addition, the tool will comprise questions about the experience of psychological, physical and sexual violence. Moreover, semi-structured interview guide will be designed for qualitative study to explore the underlying bottlenecks in the community that hinder intervention implementation.

### Data collection procedure

Data will be collected using sequential explanatory mixed method (quantitative 1 and 2, and qualitative 1 and 2) for baseline, monitoring and endline assessment. It is illustrated and attached as additional file (see Fig. 3) that is adapted from other study [71]. Face-to-face interview will be used for quantitative data collection. In-depth interview, KII and FGDs will be carried-out for qualitative study. The KII will be conducted on community representatives, district council members, women affair office, police officers, lawyers, health care providers and nongovernmental organization. Gender specific FGDs will be held on men and women to assess societal perception about domestic VAW. All participants’ socio-demographic data will be captured using anonymously coded structured questionnaire. Voice recorder, note taking and non-verbal communication during the discussion will be recorded as much as possible. An estimate of 60 to 90 min will be taken to conduct one FGD. Eventually, endline evaluation will be carried-out using the same structured questionnaire, data collectors and supervisors as of the formative assessment. Twelve female nurses, midwives or public health officers will be recruited to collect the data.

**Fig. 3 Fig3:**
[figure not shown]
diagrammatic show of the sequential explanatory mixed-method data collection process

#### Data quality assurance activities

Participants Allocation: Intervention and control group participants will be allocated based on their geographic non-proximity to minimize information contamination. In addition, regular monitoring will be carried out on both intervention and control groups.Data Collector’s Recruitment and Training: Data collectors will be recruited through consulting local leaders to get appropriate data collectors. Then, female nurses, midwives and or public health officers who have diploma or above qualification will be recruited as data collector (research assistant) to enhance quality of the data to be collected. Two supervisor who have Master of Public Health and had previous field experience will be recruited. Three days training will be given for research assistants by the principal investigator which will mainly focus on study objectives, sampling methods, data collection tool and procedures, interview techniques and ethics. Biomedical research ethical principles and WHO gender based violence research ethical guideline will be explained to research assistants. Regular supportive supervision will be given by principal investigator and supervisors.Implementers Recruitment and Training: Four community health extension workers as implementer and one supervisor will be recruited and deployed during the entire intervention period. Health extension workers who have been working in the sub-district will recruited as intervention implementer to ease integration with the existing innovative community based health extension program and working very closely with the community. Health Extension Workers (HEWs) will be re-oriented on the objectives, domestic VAW, gender inequality norm and how to integrate with their health extension package. Regular discussion and close supportive supervision will be given by principal investigator and facilitators.Pretest questionnaire: Pretest will be done on 5% of the sample size from nearby district to test sensitive words in the questionnaire, sequence of questions, sampling, data collection procedure, consent taking, interview skill and note taking. Necessary amendment will be made accordingly.Tool Development and Validation: Intervention materials will be adapted from WHO and United Nation Population Fund (UNFPA) materials, research evidence, human right protection instrument and national policy documents. Most of domestic VAW research findings recommend addressing of wife beating accepting attitude, gender norm, gender equality, women empowerment, male involvement and legal sanctions. The adapted intervention materials for community mobilization, awareness creation and training of community representatives will be peer reviewed for validation. The research team will review it and necessary modification will be made accordingly. In addition, any feedback about the material will be received from advocacy meeting participants to contextualize with the community setting.

### Data processing and statistical analysis

Both baseline and endline data will be checked and edited for completeness and consistency at field as well as at office. Explanatory and outcome variables will be clearly predefined prior to data entry, in which domestic VAW will be coded as if a woman reports at least one type of experience of either physical, psychological or sexual violence coded as “Yes = 1” and “No = 0”. Similar coding will be done for physical, sexual and psychological domestic violence against women to carry out subgroup analysis. On the other hand, women’s wife beating accepting attitude will be measured using six questions or measurements, and also if women respond at least one justifying wife beating [58, 59, 61]. Similarly women autonomy will be measured in four indicators such as economic decision-making, reproductive health service utilization decision-making, extent of freedom of movement, and women’s attitudes toward violence [54].

Then, data will be entered in Epidata (3.5.1) and exported to SPSS (23.0) for further cleaning and analysis. Multiple imputation will be done to handle missing data as necessary. Descriptive statistics, binary and multiple logistic regressions and Intention to Treat Analysis (ITTA) will be computed. Moreover, Difference in Differences (DID) will be calculated to determine the net intervention effect. Finally, statistical significance of intervention effect will be measured using adjusted prevalence ratio, adjusted odds ratio/risk ratio at 95% confidence interval (CI) and *P*-Value less than 0.05. On the other hand, qualitative data will be transcribed through playing and replaying the voice recorder and also narrating the note taken during interviews or FGDs. The voice recorder audio will be listen as much as possible in quiet place. It will be transcribed independently by research assistant and principal investigator according to the verbatim of participants'. Then transcribed qualitative data will be translated from local language (Amharic) to English. The quotes will be narrated and cited using participant’s code. Thematic areas will be identified and arranged based on their themes. Ideas will be color coded, and then merged accordingly. Qualitative data will be analyzed or arranged using Nvivo software.

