### Quantitative study participants

Married or cohabiting women (15–49 years) will be recruited for the quantitative study. Study participants will be allocated into intervention, active comparator and control groups. Three districts will be selected out of nine districts considering stability or mobility status, convenience to implement intervention and monitor the control. The study design and participant allocation is illustrated as an additional file (see Fig. 2).

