**Table Tabb:** 

Phase 1: Baseline	Phase 2: intervention implementation	Phase 3: endline	Phase 4: dissemination and scale up
-Baseline data collection -Instrument validation -Contextualization of the intervention -explore community perceptions	-advocacy meeting with local administrative bodies and stakeholders to explore implementation barriers and also enhance engagement of stakeholders -community mobilization -awareness creation to the women on gender equality, rights and community norm -awareness creation and enhance husband/partner involvement -Training of community representatives to involve them in the traditional norm change agent -traditional coffee ceremonies and community conversation	-endline data collection - statistical analysis to investigate the intervention effect between baseline and endline -identify barriers and enablers for the future domestic violence prevention	*Dissemination
			-Advocacy meeting -policy Brief -publication in peer review journals -local Media -use social media -present in conference s
			*Scale up of successful experiences
			-learn from barriers and propose alternative solutions -integrate with health extension program -engaging stakeholders/ community
M& E	M& E	M& E	
-measurement tool and intervention material validation -number of women interviewed per day and completeness and consistency of questionnaire	-number of advocacy workshop -pre-posttest of the participant -feedback from participants -number of women involve in awareness creation -number of community representatives trained and involve on community mobilization -number of husbands/involved and attend awareness creation program - implementers briefing and debriefing regular session -KII and FGD on the progress of the intervention and acceptability of the intervention by the community	-re-orientation of data collectors -use same data collectors and same site -using same household and make sure that the women is the former participant -determine prevalence of domestic VAW -identify barriers -determine difference in difference -note that; the control group will be monitored regularly on what is going on in addition to the standard care and findings will be documented using reporting checklist.	

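### Each arm is one purposively chosen district with two sub-districts, yet the effect is declared from individual women at P<0.05 with no stated allowance for community or for repeat interviews

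*Protocol article*

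**What the plan says.** **Allocation.** Under Sampling procedure: "Three districts are selected out of nine districts in Awi zone (comprehensive intervention, active comparison and control"). Under Quantitative study participants, the grounds for choice are practical: "Three districts will be selected out of nine districts considering stability or mobility status, convenience to implement intervention and monitor the control". Within districts, "six sub-districts (two sub-districts from each district) will be selected purposefully considering appropriateness for intervention, resource" and geographical separation. Nothing is randomised.

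**Delivery.** The section on advocacy and stakeholders and the arm descriptions that follow it describe work on whole communities: quarterly advocacy with local offices, mobilisation at public gatherings, training of local leaders, and house-to-house awareness work by health extension workers.

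**Sample size.** "Eventually, a total 1269 women is obtained for the three arms (i.e. 423 for each group"). This includes a design effect of 1.11, taken from a regional figure on physical or sexual violence and justified by multistage sampling.

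**Analysis.** The outcome is yes/no for each woman. Under Data processing and statistical analysis: "Descriptive statistics, binary and multiple logistic regressions and Intention to Treat Analysis (ITTA) will be computed". DID is to give the net effect. Significance is to be judged from adjusted prevalence, odds or risk ratios with 95% confidence intervals and P<0.05.

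**Repeat interviews.** The endline column of the phase table calls for "using same household and make sure that the women is the former participant".

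**The concern.** The intervention acts on communities, so the replication behind each arm is two sub-districts in one district, not 423 women. Women in one sub-district share leaders, police, churches and local events, so their answers, and the changes in them, may be correlated. An individual-level test that ignores this gives intervals that are too narrow. DID cancels stable differences between districts. It does not cancel a different course over the year, such as a local campaign, an economic shock or a change in policing. With one district per arm, such a difference has the same form in the data as an intervention effect.

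The article says that the study tests effectiveness as well as feasibility, and it plans a policy brief and scale-up. A P<0.05 that reflects a difference between places would feed those decisions.

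**Working it through.** **1. Reproduce the plan's sample size.** Inputs from Sample size determination: p = 0.22, d = 0.22 − 0.09 = 0.13, margin 0.05, z = 1.645 for alpha, 15% added, design effect 1.11. The article prints 0.845 for the power term; 0.84 is the usual rounding.

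- N = 2 × ((1.645 + 0.84)/(0.13 − 0.05))² × 0.22 × 0.78 = 331.1
- 331.1 × 1.15 × 1.11 = 422.7, that is 423 per arm. With 0.845 the result is 424.4.

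The stated figure reproduces, so 1.11 is the whole of the clustering allowance.

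**2. What 1.11 covers.** With an equal split (an assumption, since the plan allocates in proportion to size), m = 423/2 = 211.5 women per sub-district. From DEFF = 1 + (m − 1) × ICC, ICC = 0.11/210.5 = 0.0005.

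**3. Endline comparison of individuals.** The ICC is assumed. True error of a nominal two-sided 5% test = 2 × (1 − Φ(1.96/√DEFF)).

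| Assumed ICC | DEFF | Effective N per arm | True error |
|---|---|---|---|
| 0.0005 | 1.11 | 381 (423/1.11) | 6% |
| 0.005 | 2.05 | 206 | 17% |
| 0.01 | 3.1 | 136 | 27% |
| 0.02 | 5.2 | 81 | 39% |
| 0.05 | 11.5 | 37 | 56% |

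A beta-binomial simulation (two sub-districts of 211 per arm, prevalence 22%, 40,000 runs) gave 6%, 17%, 27%, 40% and 56%.

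**4. DID.** Two simple approximations bracket the problem.

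(a) Let the ICC be that of change, and suppose the two records of a woman are analysed as unpaired. The ratio of true to assumed variance is (1 − ρ) × DEFF, where ρ is the within-woman correlation (assumed).

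| ICC of change | ρ = 0.3 | ρ = 0.5 |
|---|---|---|
| 0.005 | 0.7 × 2.05 = 1.44; 10% | 0.5 × 2.05 = 1.03; 5% |
| 0.01 | 2.17; 18% | 1.55; 12% |
| 0.02 | 3.65; 30% | 2.61; 22% |
| 0.05 | 8.07; 49% | 5.76; 41% |

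(b) Ignore within-woman correlation and let sub-district levels persist with cluster autocorrelation c (assumed 0.5 to 0.9). The inflation is 1 + m × ICC × (1 − c)/(1 − ICC). At ICC 0.01 and c = 0.9 this is 1.21, error 7.5%. At ICC 0.05 and c = 0.5 it is 6.57, error 44%.

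Over ICC 0.01 to 0.05 the two give roughly 7% to 49%. At ICC 0.005 with ρ = 0.5 the two distortions nearly cancel.

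**5. Degrees of freedom.** Six sub-districts less three arms leave 3 pooled (critical t 3.18). A single pair of arms leaves 2 (critical t 4.30). With the 2-df test, power for 22% against 9% at endline is about 73% at ICC 0.0005, 39% at 0.01, 27% at 0.02 and 16% at 0.05. With district as the unit there is one per arm and 0 df, so between-district variation cannot be estimated.

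**The case against.** The best defence is that the analysis section lists families of methods, and that random effects, robust variances or repeated-measures terms are commonly left to a fuller document. Part of this stands. A reader might infer that each woman's two interviews will be analysed as if they came from different women. The article does not say so: households receive unique codes for endline use, so pairing is possible. What can be said is that no such allowance is named. The defence does not reach the core, because the article itself fixes one district per arm and the P<0.05 criterion, and no later model can separate district from arm.

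Second, the ICC is assumed. At the value implied by the plan's own 1.11, the endline error is only about 6%. This stands as a limit on size. But the 1.11 is a regional figure tied to multistage sampling, not to allocation of whole communities, and it enters the sample size, not the analysis.

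Third, the study is openly quasi-experimental and described as a pilot, DID removes stable differences, and the control group is monitored. Monitoring may identify an outside event, but it cannot remove that event's effect from the estimate.

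A reader might also conclude that P<0.05 is out of reach for any honest analysis, because permuting two against two sub-districts gives six arrangements. That argument presumes random allocation, which is absent, and a t-based interval on sub-district changes can reach P<0.05 if the effect is large.

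**Conclusion.** The concern holds in limited form. Followed as written, individual-level intervals and P<0.05 are not valid for the intervention effect unless between-community variation is near zero, and nothing in the article supports assuming that. The endline error of about 17% to 56% rests on assumed ICCs of 0.005 to 0.05 and equal sub-district sizes. Those rates should not be carried over to DID. There the range is roughly 7% to 49% at ICC 0.01 to 0.05, and it can be close to nominal at a smaller ICC with strong within-woman correlation. The confounding of district with arm needs no ICC: it follows from the allocation alone.

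**What to change.** In Data processing and statistical analysis:

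1. Specify an arm-by-time model on the stacked baseline and endline records, with the woman as the repeated-measures unit and sub-district accounted for.
2. Report the baseline-to-endline change in each of the six sub-districts.
3. Base the intervals for arm contrasts on sub-district-level changes with small-sample degrees of freedom (3 pooled), in place of individual-level P<0.05.
4. State that district is fully confounded with arm, so that even these intervals omit between-district variation. Describe the effect estimates as exploratory and as applying to these sub-districts, and show the DID interval over a range of ICCs.

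This is a change of wording and analysis, with no extra women or sites. The price is wider intervals, low power at plausible ICCs and a more modest claim. Item 3 does not cure the district confounding, which is why item 4 is needed.

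Spreading the six sub-districts over six districts would break the tie between arm and a single district, but it is not required here. It would raise the intervention districts needing quarterly advocacy from two to four, could conflict with the separation of sites, and would still leave two clusters per arm.
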